### Intervention and implementation

The BTBYCB program consists of a launch event (i.e., inspirational talk), 11 teacher led classroom sessions that are embodied and aligned with the aims and intent of the new Secondary curriculum, and a concluding Olympic celebration event. Adopting a cross curricular approach (i.e., sessions can be delivered across PE, PHSE, and other curriculum areas), the program’s aims are to (i) inspire pupils to engage with the Olympic ethos and values; (ii) help pupils gain greater self-awareness and self-responsibility; (iii) empower pupils through provision of self-regulatory skills; (iv) raise pupils aspirations and expectations for success, and (v) provide pupils with the skills, resources, and insights to face the challenges of lifelong learning and fulfillment.

As part of the BtBYCB program, the school teaching staff responsible for delivery attend a day long teacher training workshop prior to implementation of the program. These sessions are delivered by the developers of the program and held separately for each school. The training sessions include explanations of the program aims, structure and content, an introduction to the program curriculum and accompanying workbook, and lessons and advice on how to best deliver each classroom session. Teaching staff attending the teacher training session all receive a BTBYCB training manual that includes learning materials, guidelines, and instructions on how to deliver each session effectively.

In total, the BTBYCB program consists of 13 sessions. The program commences with an introductory talk and question and answer session delivered by an Olympian, Paralympian, or other high achiever. This session is designed to help pupils experience life through the eyes of a high achiever (i.e., appreciate their inner perspective), and discover the personal journey and skills required to succeed in life. The concept of Olympic and/or Paralympic achievement is then extended to the pupils, encouraging them to establish personal goals that represent success in life, and not just sport-related activities.

The eleven BTBYCB classroom sessions consist of Olympic and Paralympic themed lessons, exercises, and activities that provide pupils with the knowledge and skills necessary to realize and raise their aspirations, and ‘ask the right questions’, raising personal and social awareness. As each pupil progresses through the program they create a personal success map that records how they have realized and taken ownership of their aspirations, and created opportunities and strategies to help in achieving these aims (i.e., the aim is to enhance awareness and responsibility of self-endorsed goals and motives). The program culminates with an Olympic/Paralympic celebration, in which pupils perform a short presentation to an audience of their peers, teachers, and invited guests (e.g., the guest speaker, parents, and members of the community) on what the program has meant to them. Table 1 provides an overview of the sessions within the BtBYCB program.

**Table 1 T1:** Overview of the BtBYCB program session structure

**Session**	**Content and purpose**
1	Olympian Launch: An Olympian/Paralympian is used to inspire and motivate pupils through the story of his or her personal journey, making pupils aware of the skills, values, and work required to succeed.
2.	Visioning: Pupils reflect upon what inspires and interests them, and are encouraged to autonomously develop a vision of their future, visualizing the possibilities available to them and how they might achieve them (i.e., increasing their self-awareness).
3.	Coaching & Mentoring Skills (1). Through discussing what it means to be an effective coach or mentor and the difference between open and closed questions, pupils begin to understand the principles of self-awareness, self-regulatory processes, and responsibility and the power of effective questioning.
4.	Coaching & Mentoring Skills (2). Pupils develop and apply their questioning skills using the GROW (Goals, Reality, Options, & Will) model as a means for constructing powerful conversations regarding their future aspirations. The development of peer mentoring skills is also a focus of this session.
5.	Coaching & Mentoring Skills (3). Through group conversations pupils explore the skill and value of empathic and attentive listening, generating valuable feedback insight and support in relation to their aspirations. This session helps the pupils to take on board, and respect, the views and values of others.
6.	The Power of Alignment: Pupils develop the concept of leading a balanced lifestyle (i.e., mind, body & spirit) and are encouraged to develop a positive self-image, identifying personal strengths and planning future steps.
7.	Body - Health and Fitness: Pupils identify the factors that affect human performance, personal health, and well-being, and discuss their current reality against these factors, prioritizing personal improvements (i.e., actions, measures, and outcome).
8.	Using the Mind Effectively: Pupils explore learning strategies that use the mind for maximum effect (e.g., multiple intelligences, mind mapping, brain gym), with the purpose of developing new skills and way of thinking. This session also covers autonomous decision making.
9.	Emotions – Enhancing Relationships: Pupils identify the values and emotions that underpin their behavior and how these factors impact their relationships with others.
10.	Understanding and Harnessing the Olympian Spirit: Pupils explore the value of prosocial behaviors and how each individual can make a positive contribution to society. They identify with the value and enjoyment of everyday life and recognize the role of significant others in making positive contributions to their own lives and the lives of others.
11.	Olympian Responsibility Through Teamwork: Through group activities pupils explore the qualities that characterize high performing teams and recognize the benefits of working as an effective team.
12.	Olympian Reflection: Pupils review their work through group presentations, sharing success stories, personal aspirations, and future success maps.
13.	Olympic Celebration: Through group presentations to teachers, peers, and invited guests (e.g., the guest speaker, parents, and members of the community), pupils have the opportunity to share and demonstrate their personal progress, successes to date, and future aspirations.

### Control group

Participants in the control group attended their usual PSHE classes (i.e., they received standard care). In the main phase of the trial, the participants provided data pertaining to the study variables of interest. The measurements in the control schools were scheduled for the same time points as for the intervention group.

### Data collection

Because the participants in the proposed work were under the age of 16 years, written approval for the program evaluation was sought from headteachers who were asked to act in loco parentis. Letters were posted to all parents providing information about the study and seeking consent. To this end, only those who did not wish their child to take part were required to respond (i.e., passive content was sought). Participants also provided written consent and were informed that they could withdraw from the study at any time, without incurring any negative repercussions; the program would be delivered to all pupils in the class but participation in the evaluation research was optional.

Accelerometers (Actigraph GT1M) were issued to a subsample of pupils from the intervention and control schools (n = 103). The accelerometers were secured to the participants’ waists via an elastic belt and positioned on the midaxillary line on the right hip. Participants were provided with verbal and written instructions regarding accelerometer use and asked to wear the device each day (from waking) before removing it at night for sleep. Participants were also asked to remove the device when bathing, showering, or engaging in water based or contact sports. Participants were asked to wear the accelerometer for a period of 8 days and the devices were set to record data in 60 second epochs.

Self-report questionnaires were completed during school hours as part of a series of supervised classroom exercises. Sessions were supervised by trained research assistants and members of the schools teaching staff (e.g., headteachers, teachers, and learning support staff). Instructions for completing the questionnaires were read out to the pupils in advance of the session. Pupils were asked to raise their hand if they had any questions regarding the nature or content of the questionnaires. Members of the research team were present during the sessions to assist the participants.

During the questionnaire sessions, small groups of participants were taken to a separate room for measurements of height and weight (i.e., to avoid potential embarrassment). Height and weight were measured using standardized procedures [23]. Participants were required to remove their shoes for assessments of height and weight. Assessments were performed on an individual basis and pupils were not told their weight. Chronological age in decimals was calculated as the difference between each participant’s date of birth and date of measurement. Biological parents of the participants also provided their heights via self-report. As adults generally overestimate height, the self-reported height of each parent was adjusted for over estimation using an equation constructed from over 1000 measured and estimated heights of adults [24].

### Primary and secondary outcomes

#### Primary outcomes

*Eudaimonic well*-*being* refers to *living well* (e.g., aspiring to personal excellence, pursuing a meaningful life, contributing to the lives of others, holding intrinsic values, etc.). Changes in eudaimonic well-being were assessed both at the contextual and life-domain levels of generality cf. [25]. Because SDT provides explicit information regarding the conditions required to promote *eudaimonic well*-*being*, we also examined whether the intervention achieves its aim of promoting significant changes in a lifestyle supportive of personal growth, through facilitating need-satisfaction and autonomous enactment. While eudaimonia refers to a lifestyle, the content of the BtBYCB program is also likely to directly (and indirectly through eudaimonic well-being) foster changes in the more temporal experiences of positive well-being. These are reflective of *hedonic well*-*being* or subjective well-being, indexed by life satisfaction, the presence of positive affect, and absence of negative affect cf. [26], and were also recorded as primary outcomes. Finally, we also assessed changes in the participants’ reported level of self-esteem, self-perceptions, and patterns of adaptive learning strategies.

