### Sample size calculation

Using a sample size calculator software package [21], the 58 classes used in this work based on the average size of class (i.e., 25 pupils; [22]) permitted the detection, at the 5% significance and 90% power level, of a standard difference of 0.25 (i.e., .25 of a standard deviation can be detected with an intra-cluster correlation (ICC) of .05). In recognizing that some classes were smaller than the average 25 pupils, a more conservative estimate using the same criteria (5% significance with 90% power assuming an ICC of .05) showed that .27 of a standard deviation could be detected with 50 classes with 25 pupils in each cluster. The current sample size also accommodates analyses at school and classroom levels (i.e., pupils are nested within classes which are, in turn, nested within schools).

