### Measures

All primary and secondary outcome measures were assessed at baseline (Time 0), at the end of the intervention (Time 2), and at 3-month follow-up (Time 3). Data pertaining to theoretically-relevant variables [cf. 5,6] that may mediate changes were assessed at a mid-point data collection (week 6 of the program). The measures selected in the trial were:

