#### Primary

*Eudaimonic well*-*being* was assessed at the contextual level by the Personally Expressive Activities Questionnaire [28] and at the life-domain level by items from previously validated questionnaires (i.e., the Personal Growth subscale [29], Prosocial subscale of the Strengths and Difficulties Questionnaire [30], Subjective Vitality Scale [31], and the Proactive Attitude Scale [32]. *Hedonic well*-*being* was assessed by the Positive and Negative Affect Scale for Children [33] and Life-Satisfaction in Adolescents Scale [34]. *Self*-*esteem* was assessed by Rosenberg’s scale [35], and *adaptive learning strategies* by the Patterns of Adaptive Learning Scale [36].

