### Data Analyses

Initially, analysis of variance (ANOVA) will be conducted to establish significant differences for the primary and secondary outcome variables between the two trial arms (allowing for the effects of nesting). Effect sizes, confidence intervals and confidence levels will be calculated. Changes from baseline in the primary and secondary end-points will be analyzed using an analysis of covariance (ANCOVA) model with the intervention as the main factor and baseline as a covariate. Further, multilevel modeling (using HLM 7 software; [47]) will be used to assess the strength of the effect of the intervention on the outcome variables (both primary and secondary) when controlling for nesting effects. Class and school will represent higher order units of analysis, and individual responses the lower order unit of analysis. In such analyses, it is possible to enter class and/or school as a random effect and all other variables as fixed effects.

For the focus groups and individual interviews, the recordings will be transcribed verbatim and analyzed using interpretive phenomenological analysis [48]. Statements will be coded by the investigators and a research assistant with themes within and across participants being extracted. Dependability and trustworthiness of the analysis will be demonstrated through; (i) researcher triangulation (i.e., discussion between researchers to establish all inferences are supported by the data), (ii) the triangulation of qualitative with quantitative data [49], and (iii) participant debriefing to check the researcher’s interpretations, and allow interviewees to make further comments.

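### Ten scores are labelled primary at two unranked follow-up times, while the sample size covers a single 5% test tied to none of them

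*Protocol article*

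**What the plan says.** **Primary outcomes (Primary and secondary outcomes).** Eudaimonic well-being is assessed at two levels. Hedonic well-being is indexed by life satisfaction, positive affect and negative affect. The section then adds the pupils' "reported level of self-esteem, self-perceptions, and patterns of adaptive learning strategies".

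**Measures, Primary.** Of eudaimonic well-being the section says that it "was assessed at the contextual level by the Personally Expressive Activities Questionnaire [28] and at the life-domain level by items from previously validated questionnaires", of which four are named. Instruments follow for affect, life satisfaction, self-esteem and adaptive learning. None is listed for self-perceptions.

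**Measures, opening paragraph.** All primary and secondary measures are taken at baseline, "at the end of the intervention (Time 2), and at 3-month follow-up (Time 3"). Neither follow-up is designated as the main one.

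**Sample size calculation.** The 58 classes "permitted the detection, at the 5% significance and 90% power level, of a standard difference of 0.25". The more conservative 50-class version uses the same criteria, "5% significance with 90% power assuming an ICC of .05". No outcome or time point is mentioned.

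**Data Analyses.** ANOVA is to be used "to establish significant differences for the primary and secondary outcome variables between the two trial arms", followed by ANCOVA and multilevel models on the same variables. No significance level is stated here.

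**Aims and Hypotheses.** The constructs vary. The abstract's aim includes aspirations and self-perceptions. The Aims section drops aspirations. The well-being hypothesis names only eudaimonic well-being, hedonic well-being and self-esteem.

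**The concern.** A trial's primary claim needs a defined endpoint at a defined time. Here the label covers ten scores at two times, so up to twenty comparisons carry equal standing, and nothing on the page says which of them decides whether the program worked. Two consequences follow.

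- If the comparisons are made without adjustment, the chance of at least one spurious significant primary result is well above the 5% used in the power statement.
- If they are adjusted, the stated 90% power for 0.25 SD no longer applies, because that figure is for a single test.

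The shifting list of constructs adds to the difficulty. A reader of the eventual report could not tell which outcomes the primary claim was meant to cover, and could not rule out that an outcome or time was chosen after the event.

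**Working it through.** **1. Count of primary scores with a listed instrument** (Primary outcomes; Measures, Primary)

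| Domain | Scores |
|---|---|
| Eudaimonic, contextual level | 1 |
| Eudaimonic, life-domain level (personal growth, prosocial, vitality, proactive attitude) | 4 |
| Hedonic (positive affect, negative affect, life satisfaction) | 3 |
| Self-esteem | 1 |
| Adaptive learning, counted as one score | 1 |
| Total | 10 |

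Self-perceptions is left out of the count because no instrument is listed. Two follow-up times give 10 × 2 = 20 comparisons.

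**2. Reproducing the plan's own figure**

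Inputs from Sample size calculation: 58 classes of 25, ICC 0.05, 5% significance, 90% power. Equal arms are taken from the 1:1 allocation of schools. Two-sided testing is assumed because it fits the stated figure; a one-sided test would give 0.228 SD.

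- Design effect = 1 + (25 − 1) × 0.05 = 2.2
- Effective n per arm = 58 × 25 / 2 / 2.2 = 329.5
- Standard error of the standardised difference = √(2 / 329.5) = 0.0779
- Detectable difference = (1.960 + 1.282) × 0.0779 = 0.2525 SD, stated as 0.25
- Power at 0.25 SD = 89.4%

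The same steps with 50 classes give 0.272 SD, stated as 0.27. Both figures reproduce, and both are for one test at 5%.

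**3. Chance of at least one significant primary result when the program has no effect**

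Assumption: each score is tested once per time, unadjusted, at two-sided 5%, so 2.5% in the favourable direction.

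Independent tests:
- Ten, one time: 1 − 0.95^10 = 40.1%; favourable only, 1 − 0.975^10 = 22.4%
- Twenty, both times: 1 − 0.95^20 = 64.2%; favourable only, 1 − 0.975^20 = 39.7%

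Correlated tests were simulated as normal test statistics with a common correlation between outcomes and 0.6 between the two times. All these correlations are assumed, since the document gives none.

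| Correlation between outcomes | One time, either direction | Both times, either direction | Both times, favouring program |
|---|---|---|---|
| 0.3 | 35% | 54% | 28% |
| 0.5 | 29% | 45% | 23% |
| 0.7 | 21% | 34% | 17% |

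**4. Cost in power of keeping all ten as primary at one time**

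Bonferroni level = 0.05 / 10 = 0.005, critical value 2.807.

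- Power at 0.25 SD = Φ(0.25 / 0.0779 − 2.807) = 65.6%
- Difference detectable with 90% power = (2.807 + 1.282) × 0.0779 = 0.32 SD

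Holm is never less powerful than Bonferroni, so these are floor values for it.

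**The case against.** The strongest reply is that this is a condensed article with no analysis plan shown. A multiplicity rule could well sit in that plan. The 5% level appears only in the sample size section, and the analysis section also promises effect sizes and confidence intervals. All of that stands, so the absence of a family-wise rule is not itself the point, and the error rates above are conditional.

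A reader might infer that a false claim of effectiveness is close to a coin flip. The document does not support that. Nowhere does it say that one significant result counts as success, and its hypotheses are directional. The figures near one half count results in either direction; for a result favouring the program the range is 17% to 28% with correlated outcomes. Even the independence figure of 40% is an upper case, since overlapping well-being scales completed by the same pupils are unlikely to be independent.

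A reader might also count eleven outcomes and 22 tests. The eleventh, self-perceptions, has no listed instrument and cannot be counted as a test.

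It can further be said that a standardised difference suits any continuous scale, and that the well-being hypothesis narrows the field to three constructs. Both are true, but neither selects an endpoint or a time. Those three constructs still span nine scores.

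What survives is that the article itself sets out the primary set. Choosing the primary endpoint and powering the trial on it belong to the protocol, and a later multiplicity rule would not restore the stated power.

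**Conclusion.** The point holds in a limited form. The primary set is fixed badly: ten scores, two unranked times, one further construct without an instrument, and a power calculation for a single 5% test attached to none of them.

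Under unadjusted 5% testing of the ten scores at both times, the chance of at least one significant result under the null is about 34% to 54% (64% if independent) against a nominal 5%. For a result favouring the program it is about 17% to 28% (40% if independent) against a nominal 2.5%. These ranges rest on assumed between-outcome correlations of 0.7 to 0.3, an assumed 0.6 between times, and one test per outcome and time. Choosing among the three planned types of model would raise them.

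The lack of a named endpoint and time, and the mismatch with the power statement, do not depend on those assumptions.

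**What to change.** Before outcome data are analysed by arm:

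1. Name one primary outcome, or a small co-primary set with Holm, at one time point. Tie the 0.25 SD to it. With a single primary outcome, power at 0.25 SD stays at about 89% on the protocol's own inputs.
2. Make the remaining scales and the other time point secondary.
3. If all ten scores must stay primary, apply Holm at one time point and restate the detectable difference: at the Bonferroni level of 0.005, about 66% power at 0.25 SD, or about 0.32 SD at 90% power.
4. Remove self-perceptions from the primary claims unless an instrument was collected, in which case list it. Align the construct lists in the abstract, Aims, Hypotheses and outcome sections.

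No new data are needed. The cost is that fewer outcomes can be called confirmatory. The article reports data collection in the past tense and the quantitative analysis in the future tense, so the record should state that the choice was made without sight of results by arm. If that cannot be shown, the choice should not be presented as prespecified.

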#### Secondary outcomes (health-related)

The content of the BtBYCB program embraces messages pertinent to pursuing a healthy lifestyle and encompasses activities that require pupils to evaluate, reflect, and take ownership of improving their health status. As such, in the present work we also tested whether the intervention promoted positive changes in reported levels of a number of modifiable health-risks; namely physical activity level, dietary intake, tobacco use, and alcohol consumption. In addition to direct changes, it is likely that changes will be mediated by increases in eudaimonic well-being as this index of well-being has been positively linked with physical health and mortality [27]. Finally, pupils within a randomly-selected subsample of school classes balanced across the conditions wore an accelerometer to objectively assess changes in weekly physical activity level at one week before and after the intervention, and at 3-month follow-up (n = 103 pupils). Body-mass index (BMI) was also obtained from most participating pupils and will be expressed as age-adjusted.

